## 5. Trial Population

### 5.1. Screening data

Screening data is not collected in the eCRF but the number of screened patients will be calculated from screening logs.

### 5.2. Eligibility

Inclusion and exclusion criteria are defined in the study protocol. Data about reason for non-inclusion is not documented in the eCRF and will not be available.

### 5.3. Patient flow

A CONSORT patient flow diagram will be drawn following the CONSORT 2010 standards.

### 5.4. Withdrawal/loss to follow-up/drop-outs

All withdrawals, drop-outs and losses to follow-up will be listed with time points and reasons (if available).

### 5.5. Baseline patient characteristics

Evaluations of the baseline characteristics will be based on the FAS data set. They will be presented in a descriptive summary table by intervention group. Continuous variables will be shown as mean and standard deviation or median and quartiles, categorical variables as absolute and relative frequencies. No statistical comparisons of patient characteristics at baseline will be performed.

## 6. Analysis

Baseline characteristics:

Preoperative patient data such as age, sex, BMI (body mass index), neurologic examination (GCS, modified Rankin Scale (mRS), Glasgow Outcome Scale (GOS), neurological symptoms (headaches, vomitus, coma, gait disturbances, dementia, urinary incontinence, motor deficit, sensory deficit, aphasia, delir, others), underlying disease causing hydrocephalus, will be collected and summarised for both groups.

### 6.1. Outcomes

Primary outcomes:

- Surgical intervention time («Beginn oper. Vorbereitung (Lagerung)» to «Naht neurochirurgischer Teil») in minutes, plus additional 5 minutes in the stereotactic navigation group

Secondary outcomes:

- Operation time in minutes (time in minutes from “Schnitt” to “Naht”)
- Anaesthesia time in minutes (time in minutes from “Beginn Anästhesie” to “Ende Anästhesie”)
- Number of puncture attempts
- Catheter placement (optimal vs. not optimal, grade I to IV)
- Volumetry of side ventricles pre- and postoperatively in cm^3 (number and relative change)
- Evan’s Index pre- and postoperatively (number and relative change)
- Complications (infection, bleeding, complications ass. with navigation method), mortality
- Revision surgery (yes/no) and reason for revision

Outcome definitions :

The primary endpoint is the surgical intervention time. This is the time spent in the OR by the surgeon and includes the preparation time together (patient positioning, head clamping in the stereotactic navigation group) with the operation time of the neurosurgical part. Beginning (“Lagerung”) and ending (“Naht neurosurgical part”) of this time interval is clearly defined and will be in a standardized manner recorded by blinded anaesthesiologists. In the stereotactic navigation group, an additional 5 minutes will be added to the surgical intervention time for the preplanning of the navigation the day before the operation on the Brainlab workstation.

The optimal catheter placement has been defined as free-floating within the CSF without touching the ventricle wall or septum pellucidum, and the tip of the catheter located at the foramen of Monro showing an optimal length of the catheter. Catheters that did not fulfill all criteria have been defined as not optimally placed. Positioning of catheters will be further graded according to Yim et al. into grades I to IV (grade I: catheter terminates in the ipsilateral frontal horn, grade II: catheter terminates in contralateral frontal horn, grade III: catheter terminates in non-targeted CSF spaces, grade IV: catheter terminates intraparenchymally).

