## 1.2. Objectives

The objective of this study is to analyse the feasibility and safety of Ultrasound-guided (US-G) Ventriculoperitoneal shunt (VPS) placement. The primary objective of the study is to compare the surgical intervention of VPS placement between US-G and stereotactic navigated placement plus additional 5 minutes.

The Null-hypothesis is that there are no differences in the surgical intervention time (plus additional 5 minutes in the stereotactic navigation group) between the two methods. The Alternative Hypothesis is that US-G VPS placement has a shorter surgical intervention time compared to stereotactic navigated VPS placement.

$$H_0: \text{Time}_{US-G} = \text{Time}_{\text{Stereotactic}} + 5\text{min}$$

$$H_1: \text{Time}_{US-G} < \text{Time}_{\text{Stereotactic}} + 5\text{min}$$

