### 8.3 Dose / Device modifications

- In case of very small ventricular width based on the surgeon's individual judgement one can decide to use stereotactic navigation instead of US navigation. Due to preoperative planning and necessity of a CT scan at admission this crossover has to be done preoperatively. Vice versa, there is the possibility to intraoperatively crossover from stereotactic navigation to US navigation in case of unsuccessful placement with stereotactic navigation (e.g. in cases with new mass effect compared to the preoperative CT scan and distorted ventricular anatomy).

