## 9.2. Assessments of outcomes

### 9.2.1. Assessment of primary outcome

Primary outcome (surgical intervention time) will be recorded for every operation by anaesthesiology, as it is standard in our department. This time spans the time spent in the OR by the neurosurgeon, beginning with any intervention on the patient (e.g. positioning, head clamping) and ends when the neurosurgical part of the operation is finished, so it consists of the preparation time, and the operation time of the neurosurgical part of the operation together. To minimize bias, the visceral surgery part of the operation (laparoscopically assisted insertion of the peritoneal catheter intraperitoneally) will not be included into this time interval.

[figure not shown]

**Figure 1: Composition of the surgical intervention time (preparation time plus operation time neurosurgical part), plus additional five minutes in the stereotactic navigation group.**

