## 11 STATISTICAL METHODS

### 11.1 Hypothesis

The hypothesis of the study is that patients undergoing VPS placement using US navigation have a shorter surgical intervention time than patients undergoing VPS placement using stereotactic navigation.

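### The primary outcome adds an unmeasured 5 minutes to the stereotactic arm, and no analysis of recorded time without it is planned, so a significant result alone does not show shorter recorded time.

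*Combined protocol and SAP*

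**What the plan says.** SAP 6.1 defines surgical intervention time as an interval recorded by anaesthesiology, from the start of positioning (Lagerung) to the neurosurgical suture (Naht): "This is the time spent in the OR by the surgeon". Protocol 9.2.1 agrees: "This time spans the time spent in the OR by the neurosurgeon". SAP 6.1 and protocol 5.1 then add the constant: "In the stereotactic navigation group, an additional 5 minutes will be added to the surgical intervention time for the preplanning of the navigation". That planning is done at a workstation the day before or, in emergencies, directly before surgery (protocol 3.2). Protocol 8.8 places the workstation in the hospital library.

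SAP 1.2 carries the constant into the test. The null is that "there are no differences in the surgical intervention time (plus additional 5 minutes in the stereotactic navigation group) between the two methods", and the alternative is Time(US-G) < Time(stereotactic) + 5 min. SAP 2.1 and 2.4 call this superiority. Protocol 11.1 gives the hypothesis without the constant: "patients undergoing VPS placement using US navigation have a shorter surgical intervention time than patients undergoing VPS placement using stereotactic navigation".

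Three things are not stated:
- No source is given for the value 5, and planning duration is not among the variables listed for the admission and operation-day visits (protocol 9.3.1, 9.3.2).
- SAP 6.3.1 has no analysis of recorded time without the constant.
- SAP 2.3 and protocol 11.2 do not say whether the 15-minute target includes the 5.

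**The concern.** The rationale for ultrasound guidance is operating-room cost and time under anaesthesia (protocol 3.6 and 4.2). Planning done the day before in another room uses neither. Part of the primary difference is nevertheless set by assumption, in one arm only, and the direction favours the experimental method.

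On recorded time, the SAP's alternative is true whenever ultrasound is less than 5 minutes slower in truth. That has the form of a non-inferiority hypothesis with a 5-minute margin. What is at stake is the sentence the trial may write: a significant primary result would naturally be reported as shorter surgical intervention time, and the planned analysis does not establish that for the recorded interval.

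**Working it through.** **Inputs.** SD 28.65 min, target difference 15 min, power 80%, 58 evaluable per group, 1% drop-out and 5% non-adherence (SAP 2.3; protocol 11.2). Two-sided 5% test (SAP 4.2). Randomised size is 65 per group in SAP 2.3 and 68 per group in protocol 11.2, so both are used. Assumptions: equal SDs in both arms, no covariate gain, no crossover.

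**1. Reproduce the plan's figure.** n = 2(1.960 + 0.842)² × 28.65² / 15² = 57.3, rounded up to 58 per group, as stated. Inflation: 58 / 0.99 / 0.95² = 64.9, so 65, as in the SAP. The inputs are therefore read correctly.

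**2. Standard error of the difference**, SE = 28.65 × √(2/n):
- n = 58: 5.320
- n = 65: 5.026
- n = 68: 4.913

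**3. Chance of a significant result favouring ultrasound** when ultrasound is truly k minutes slower on recorded time: P = Φ((5 − k)/SE − 1.960). For k = 0 and n = 68: Φ(5/4.913 − 1.960) = Φ(−0.942) = 17.3%.

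| True recorded disadvantage of ultrasound (min) | 65 per group | 68 per group |
|---|---|---|
| 0 | 16.7% | 17.3% |
| 1 | 12.2% | 12.6% |
| 2 | 8.6% | 8.9% |
| 3 | 5.9% | 6.0% |
| 4 | 3.9% | 4.0% |
| 5 | 2.5% | 2.5% |

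With 58 evaluable per group the first row is 15.4%. Using the t distribution lowers the first row by about 0.2 points. If covariates explained 10 to 30% of the variance (an assumption), it would rise to about 18-22% (65 per group) or 19-23% (68 per group). A test on recorded time gives 2.5% in the first row.

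**4. What must be observed.** The unadjusted test needs a difference of 1.96 × SE, of which the constant supplies 5 minutes:
- n = 65: 9.85 − 5 = 4.85 min observed advantage on recorded time
- n = 68: 9.63 − 5 = 4.63 min

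**5. Power on recorded time, without the constant**, before losses and crossover:
- If the 15 minutes is recorded time: 84.7% (65) or 86.3% (68).
- If the 15 includes the 5, leaving 10 recorded minutes: 51.2% (65) or 53.0% (68). For 80% power, 2(1.960 + 0.842)² × 28.65² / 10² gives 129 evaluable per group.

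**The case against.** The constant is disclosed. It stands in the hypotheses, the outcome definitions, the synopsis and protocol 6.1, and protocol 11.1 may simply be using the defined term as shorthand. Planning is real work needed in one arm only, so total surgeon time including planning is a defensible outcome. This stands, and it is why the primary outcome need not be replaced. It would be a stronger defence if the planning were measured and the outcome were not described as operating-room time.

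Several stronger readings are tempting and are not supported:
- *The type I error is inflated to 17%.* Under the trial's own null the error in that direction is 2.5%. The 17% applies only to reading the result as shorter recorded time.
- *Ultrasound could win while observed to be slower.* The 5 minutes concern true means. An observed disadvantage could be significant only if the residual SD fell below about 14.5 min (65 per group) or 14.9 min (68 per group).
- *Crossover makes the constant seriously unfair.* Protocol 8.3 says that, before surgery, "one can decide to use stereotactic navigation instead of US navigation", and such a patient stays in the ultrasound arm without the 5 minutes. If 1 to 5% switched this way (an assumption; SAP 2.3 gives 5% for the opposite direction), the ultrasound mean would move by 0.01 × 5 = 0.05 to 0.05 × 5 = 0.25 min.
- *Dropping the constant costs no power.* The documents do not say whether the 15 minutes includes the 5.

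Anaesthesia time and incision-to-suture operation time are secondary outcomes without the constant, so the anaesthesia rationale is tested directly. Neither is the interval from positioning to neurosurgical suture: operation time omits positioning and clamping.

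A reader can also subtract 5 from the estimate and both confidence limits. That is correct for an untransformed linear model. SAP 6.3.1 allows a transformation or another model if the outcome is not normally distributed, and the subtraction then fails.

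**Conclusion.** The point holds as a gap between what is tested and what the protocol's hypothesis says. The planned test answers a question about recorded time plus an assumed 5 minutes of planning, and answers it validly. It does not by itself answer whether recorded surgical intervention time is shorter, and no planned analysis does.

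For someone drawing that second conclusion from a significant result, the error rate at equal true recorded times is about 17% at either randomised size, or 15% with 58 evaluable, instead of 2.5%. These figures rest on the pilot SD of 28.65 min holding in both arms, with no covariate gain and no crossover.

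**What to change.** 1. In SAP 6.1 and 6.3.1, pre-specify the same regression model on recorded time from Lagerung to Naht, without the constant, reported beside the primary result. Impute recorded time once and add the constant afterwards, so that both analyses use the same data.
2. State that a claim that ultrasound shortens surgical intervention time may be made only if the 95% CI of the recorded-time analysis excludes zero in favour of ultrasound. On the untransformed minute scale this is the same as the primary CI lying wholly beyond −5 min. A recorded-time success on that scale implies a primary success, so no alpha adjustment is needed. Otherwise, describe the result as time including an assumed 5 minutes of planning.
3. If the outcome is transformed or the model changed, base the claim on the analysis without the constant.
4. State in SAP 2.3 and protocol 11.2 whether the 15-minute target includes the 5.

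The cost is a few sentences and one more model run, with no new data and no change of primary outcome. The last point matters because protocol version 3.4 is dated 20.08.2024 and the last participant out is planned for 02/2025. Replacing the outcome that late could count as a substantial amendment, which needs approval (SAP 4.3; protocol 2.9). The downside is power for the recorded-time claim: if the 15 minutes includes the 5, it is only about 51-53%, and the sponsor should know this before analysis.

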### 6.3. Analysis methods

#### 6.3.1 Primary analysis

Analysis of the primary endpoint will follow the intention-to-treat (ITT) principle. It will be based on the FAS with missing data of the primary outcome imputed as described in the section “Missing data” (section 6.4). Patient data will be analysed according to their intervention allocation, irrespective of actual treatment received.

The primary outcome, surgical intervention time, will be assessed using a linear regression model. The estimates will be reported with 95% confidence intervals (CI). Explanatory variables will be BMI, underlying diagnosis, experience surgeon and the use of an old burr hole.

In case the outcome variable is not normally distributed, data will be transformed or a different model, depending on the distribution of the data, chosen.

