| Randomisation:                                                                                                                                                                                                                                                                                                                                                                                                                                                                                                                                                                                                                                                                                                                                                                                                                                                                                                                                                        | 
 
- 1:1 randomisation, stratified according to age of the patients (under 40 years/over 40 years)
 
- Randomisation via REDCap usually one day preoperatively (elective surgery), or directly preoperative (semi-emergency surgery)
 
                                                                                                                                                                                                                                                                                                                                                                                                                                                                                                                                                                                                                                           |

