## 6. STUDY DESIGN

### 6.1 General study design and justification of design

- This is a prospective, randomized controlled study in a superiority fashion. The primary outcome (surgical intervention time) is well standardized and recorded by anaesthesiology for every operation. Some of the secondary outcomes are measured by a blinded neuroradiologist. The method of randomisation is 1:1. We chose this study design, in order to achieve evidence of the best quality while minimizing possible bias.

Patients will be randomized in two groups at admission in a 1:1 rate: US or stereotactic navigation group. Randomisation will be stratified for age (under 40 years vs. over 40 years). On the day of the elective operation, the VPS will be placed with the randomized navigation method. The patient is blinded for the navigation method, but there is no possibility to perform this study in a double-blinded fashion since the surgeon cannot be masked to the method. All patients in the stereotactic navigation group need to have a CT scan that is not older than 5 days counted backwards from the operation day. In the US navigation group there will be performed a new CT at admission if the old scan (CT or MRI) is older than 90 days. In patients allocated to stereotactic navigation the entry point, trajectory, and length of the catheter will be pre-planned the day before the operation on the 1 to 5 days old CT scan. The patients allocated to US navigation will not receive any pre-planning.

All adult (> 18 years) patients receiving a VPS in an elective, semi-elective, or urgent manner will be included in the study. These patients suffer from different forms of hydrocephalus (e.g. hydrocephalus internus (malresorptivus, occlusivus), hydrocephalus externus, hydrocephalus communicans, normal pressure hydrocephalus) due to different diseases, thus creating a heterogeneous population. For each group we plan to include 65 patients, giving a total of  $130 + 6 = 136$  patients and hence a study duration of 4 years.

The primary outcome (surgical intervention time) is recorded in a standardized manner by anaesthesiology for every operation in our department. In the stereotactic navigation group, 5 minutes will be added to the surgical intervention time accounting for navigation preplanning. Some of the secondary outcomes (catheter placement (optimal vs. not optimal, grade I to IV), volumetry of side ventricles, Evans' Index) will be analysed by a blinded neuroradiologist.

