### **6.2.2 Blinding procedures**

- Participants will be blinded for the navigation method they are randomized to. There is no possibility to blind the treating physician since he has to place the VPS with the selected navigation method and stereotactic navigation needs a pre-planning the day before the operation. The primary outcome is recorded by the anaesthesiology (not involved doctor), and some of the secondary outcomes will be measured by a blinded neuroradiologist who does not know the selected navigation method.

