### 7.3 Assignment to study groups

All patients entering the hospital for elective or emergent VPS surgery will be randomized in 1:1 fashion to one of the study groups at admission or the day before the operation. The randomisation process is further described in chapter 6.2.1. and will be performed by one of the trained physicians using the REDCap software.

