Following dural opening, real-time US navigation is done holding the US probe in the coronal plane (Figure 7), showing a cross-section through both frontal horns. Saline irrigation is applied to achieve better contrast. The inline trajectory (Figure 7, in yellow) is used as guidance for positioning of the ventricular catheter with the tip at the foramen of Monro, then Foramen Monro and Choroid plexus are visualized, and the catheter is inserted. After positioning of the proximal catheter, under real-time visualisation (Figure 8), the US probe is removed, the catheter is shortened and connected to the burr-hole reservoir. The remaining procedure is similar to any other VPS placement, where the valve is connected to the burr hole device and the distal catheter, which is then implanted laparoscopically into the abdomen.

The physicians are already trained in the use of the US burr hole probe since it has been in use for many other operations, and VPS as well as EVD placement before. The operation will be performed by a trained neurosurgeon or by an advanced resident under supervision.

[figure not shown]

Figure 2: Connection of the valve and the peritoneal catheter to a large burr hole reservoir.

Figure 3: Positioning and covering of the patient for standard right frontal VPS placement (head left, abdomen right).

Figure 4: Placement of the burr hole, enlargement to the lateral side.

[figure not shown]

Figure 5: US burr hole probe attached to the guidance tool for the ventricular catheter, adaptable for the exact diameter of catheter (disposable material, single-use).

Figure 6: Image of the diameter of the US burr hole probe together with the attached guidance.

Figure 7: Real-time US navigation showing a coronal plane presenting both frontal horns of the lateral ventricles and the trajectory for catheter placement (in yellow).

Figure 8: Real-time US navigation showing a coronal plane presenting the catheter (hyperintense) entering the ventricle along the trajectory (in yellow).

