### 8.2.2 Control Intervention

Patient in the stereotactic group need to have a CT scan that is not older than 5 days counted backwards from the operation day.

The exact location of the entry point, the trajectory, and the length of the catheter will be pre-planned on the newest CT at a Brainlab Workstation using cranial navigation software version 3.1. (Brainlab AG, Munich, Germany). After intubation the head of the patient will be fixed in a Mayfield head clamp slightly rotated to the contralateral side of the operation. Before starting the operation, the navigation will be registered. After that the incision will be marked at the pre-planned entry point. The distal shunt parts are also connected directly before the start of the operation.

For placement the ventricular catheter will be inserted with the navigated stylet exactly along the planned trajectory. After functional control the catheter is cut in the precalculated length, and connected to the distal shunt parts. The other steps of the operation are exactly the same as described above for US-G VPS placement.

The physicians are already trained in using the Brainlab navigation since it is in use for almost every craniotomy and for biopsies. The operation is performed by a trained neurosurgeon or by an advanced resident under supervision.

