### 9.3.2 Visit 2: Operation day

Primary outcome (surgical intervention time), shunt side (right, left), shunt location (frontal, occipital), ventricular catheter length, number of surgeons, experience of main surgeon, shunt/valve manufacturer, type of valve (adjustable, non-adjustable), valve pressure, number of accessory incisions, shunt dysfunction, revisions surgery, indication for revision, secondary outcomes (operation time, anaesthesia time, number of puncture attempts, complications including complication details), death including reason of death.

Number of surgeons, experience of main surgeon, number of accessory incisions, number of puncture attempts are the only measurements done for the study, all the other measurements are generally assessed for all patients receiving this operation.

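### The primary model adjusts for re-use of an old burr hole, a choice made after unblinded allocation; a Visit 1 history variable should replace it, with sensitivity analyses for the operation-day covariates

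*Combined protocol and SAP*

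**What the plan says.** SAP section 6.3.1 specifies a linear regression of surgical intervention time: "Explanatory variables will be BMI, underlying diagnosis, experience surgeon and the use of an old burr hole". Section 6.3.1.2 carries the same list into the secondary models if numbers allow. Protocol section 11.4.2 leaves the choice of risk factors to the SAP. Neither surgeon experience nor burr-hole use is among the baseline characteristics in SAP section 6.

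On timing, Protocol section 7.3 says that patients "will be randomized in 1:1 fashion to one of the study groups at admission or the day before the operation". Section 6.2.2 says of masking: "There is no possibility to blind the treating physician since he has to place the VPS with the selected navigation method".

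On access to the ventricle, Protocol section 6.1 states: "In patients allocated to stereotactic navigation the entry point, trajectory, and length of the catheter will be pre-planned the day before the operation". The ultrasound arm has no pre-planning. Section 8.2.1 describes a large burr hole made after skin incision and widened laterally until the catheter passes beside the probe.

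On the operator, section 8.2.1 says "The operation will be performed by a trained neurosurgeon or by an advanced resident under supervision", and section 8.2.2 says the same for the control arm. Section 9.3.2 puts experience among the operation-day data: "Number of surgeons, experience of main surgeon, number of accessory incisions, number of puncture attempts are the only measurements done for the study".

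Use of an old burr hole is in none of the visit lists. Section 9.3.1 does list earlier external drains, shunts and head operations, with details, at Visit 1.

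**The concern.** A covariate fixed before randomisation cannot be affected by allocation, so adjusting for it is safe. A covariate that arises afterwards can be affected, and two things may then go wrong.

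First, it may lie on the path from method to outcome. One arm enters at a point planned on CT; the other needs a hole wide enough for a probe and guide channel. If this makes one method more able to use an existing hole, the time gained or lost is part of that method's effect, and adjustment takes it out.

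Second, the covariate may depend on both the arm and an unmeasured feature of the case, such as difficulty. Comparing patients with the same covariate value then compares cases of different difficulty, and a difference can appear where none exists.

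The first problem concerns the burr hole. The second could affect either variable. Surgical time is the primary outcome, so either would act directly on the trial's main result.

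**Working it through.** **The plan's own figure.** From SAP section 2.3: difference 15 min, SD 28.65 min, power 80%. From section 4.2: two-sided 5%.

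n per group = 2 × (1.960 + 0.842)² × (28.65/15)² = 57.3, so 58, as stated. The recruited number follows as 58/0.99/0.95² = 64.9, so 65 per group. No gain from covariates enters, so changing a covariate leaves the sample size alone. At 65 per group the standard error of the unadjusted difference is 28.65 × √(2/65) = 5.03 min.

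**Effect removed by adjusting for burr-hole use.** In a linear model, the amount removed is the minutes saved by an old hole multiplied by the difference between arms in the proportion using one. The documents give neither, so both are assumptions.

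- Illustration: 10 × 0.15 = 1.5 min; 1.5/15 = 10% of the target; 1.5/5.03 = 0.30 standard errors.
- Low: 5 × 0.10 = 0.5 min (3%).
- High: 20 × 0.30 = 6.0 min (40%).

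A 15-point gap needs at least 0.15 × 65 = 9.75, about 10 patients in one arm, to re-use a hole. A 30-point gap needs about 20. The eligibility criteria exclude revisions at the same side and location, which makes the high end less plausible. The direction is unknown, because the documents do not say which method would re-use holes more often.

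**Bias from adjusting for a covariate chosen after allocation.** A large-sample simulation used 1,000,000 patients per scenario, a true arm effect of zero and total SD 28.65. Unmeasured difficulty explained 10% or 25% of the variance. A yes/no covariate was worth 0 or 15 min. Rejection rates are two-sided at 65 per group, by normal approximation.

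| Choice depends on | Covariate worth | Gap between arms | Unadjusted shift (min) | Adjusted shift (min) | Rejection rate, adjusted |
|---|---|---|---|---|---|
| Not on arm | 0 or 15 | 0 | about 0 | about 0 | 5.0% |
| Arm only | 15 | about 20 to 40 points | −3.16 to −6.02 | about 0 | 5.0% |
| Arm and difficulty | 0 | 12 to 34 points | about 0 | −1.31 to −4.35 | 5.8% to 14.2% |
| Arm and difficulty | 15 | 12 to 34 points | −1.87 to −5.13 | −1.36 to −4.51 | 5.9% to 14.9% |

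The adjusted shift of 1.3 to 4.5 min is 9% to 30% of 15 min. In the third row, adjustment creates the whole shift. In the last row it sometimes helps (−2.70 becomes −1.39) and sometimes harms (−3.86 becomes −4.51). The documents do not show which row applies.

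**The case against.** The strongest reply concerns the surgeon. If operator choice depends on arm alone, the planned covariate is the remedy: the second row of the table shows it returning the estimate to zero. That stands, and it is why surgeon experience need not leave the primary model.

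A reader might go further and infer that operator imbalance inflates the error rate. With residents 20 min slower and a 15-point gap, the shift is 3 min; at the Protocol's 68 per group the standard error is 28.65 × √(2/68) = 4.91 min, and the chance of a false significant result in the favoured direction rises from 2.5% to 8.9%. That describes an analysis without the experience covariate, which the SAP does not plan.

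A reader might also infer that the main surgeon is chosen after allocation. The documents say only when experience is recorded. No rule fixes the operator beforehand, but none shows a later choice. Operator requirements are the same in both arms, and sections 8.2.1 and 8.2.2 describe physicians as already trained in each method.

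For the burr hole, the sponsor could say that the variable means a feature of the patient. If every existing hole were used regardless of arm, it would behave like a baseline value. The wording is about use, however, and the access steps differ by arm. The exclusion of same-side, same-location revisions does limit re-use, though earlier drains and other head operations are not excluded. Nor does absence from the visit lists show that the variable is uncollected: the case report form is an appendix not included in the text.

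**Conclusion.** The point holds for the burr hole. Its use follows an allocation known to the surgeon, plausibly depends on the method, and enters the primary model where a pre-randomisation substitute is available. The 1.5-min illustration rests on assumed inputs, as does the 0.5 to 6.0 min range, and the true amount may be near zero if re-use is rare or equal between arms.

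For surgeon experience the conclusion is conditional. Adjustment helps if choice depends on arm alone, has no effect on bias if choice does not depend on arm, and can bias the estimate if choice depends on arm and unmeasured difficulty. That calls for a sensitivity analysis; it does not justify removing the covariate. This is a cheap improvement, and the documents do not show that the primary comparison is invalid.

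**What to change.** In SAP sections 6.3.1 and 6.3.1.2:

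1. Replace burr-hole use with a yes/no variable from Visit 1: an existing burr hole or, failing that, a prior external drain, shunt or head operation. Derive it from the history in both arms, because the age limits for the preoperative scan differ by arm.
2. Report actual burr-hole use and operator experience by arm, descriptively.
3. Present the primary estimate with and without the operation-day covariates (surgeon experience, actual burr-hole use) as a prespecified sensitivity analysis.

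Substituting a planned surgeon's experience for the actual value is not recommended. If operators changed by arm after allocation, the planned value would stay balanced and leave that shift in the estimate. It would also come late: the protocol version is dated 20.08.2024 and last participant out is planned for 02/2025, so with a six-month final visit the last operations fall around August 2024.

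The cost is a short SAP edit, using history already listed at Visit 1. The history variable may predict time slightly less well than actual use. The sample size is unaffected.
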